## 4 STUDY PLAN

This feasibility study uses a longitudinal design and multiple methods to determine the possibility of using the MTM-Kids study processes and intervention in a future full-scale RCT. The study site will be UNC Healthcare's NC Basnight Cancer Hospital Pediatric Oncology Clinic.

### 4.1 Study Intervention

We will enroll 5 adolescent + 5 parents (5 dyads) in the formative test, and then 10 adolescents + 10 parents (10 dyads) in the validation test for a total of 15 adolescents and 15 parents. The sample size is based on evidence that testing with 5 users identifies 85% of barriers and facilitators to accessing program materials and putting them to use to inform refinements, and 3 iterations of feedback per user during the testing period identifies 98% [47, 48] Thus, we expect that 15 dyads total with 3 iterations of feedback via semi-structured interviews with the adolescent and also with the parent over the 12-week study period will provide sufficient data to uncover aspects of study processes and the program materials that need refinement prior to efficacy testing. For the formative and evaluative tests, we will use unique sets of dyads to gain a broader perspective than is possible with the same sets. We will also focus on children in the adolescent age group (ages 12-17.9 years) for this more in-depth data collection because they are more likely than younger children to express opinions independent of parental influence.[49]

Equiti Foods will tailor flavorings and deliver selected meals along with condiments to enable individualization by household members. The intervention will be 12-weeks duration, with weekly "doses" (meal deliveries) of up to 10 meals per week, as suggested by MTM studies with adult populations. [32, 44] Twelve weeks duration enables three iterations of feedback about the prior month's experience with MTM-Kids.

Participation will require (a) completing a survey at baseline (T1), receipt of MTM-Kids over 12 weeks, (b) participating in interviews at 4, 8, and 12 weeks (T2, T3, T4) after starting to receive meals to inform refinement, and (c) completing a follow-up survey at 12 weeks (T4). While we will not ask participants to forgo other forms of food-related assistance, we will ask them to tell us about food assistance requested and received. Interested dyads will join the informed consent/assent process, complete baseline surveys, and set up an account on Equiti Food's website where they can select/order the first MTM allotment.

Adolescents and parents will also be asked to participate in three audio-recorded individual semi-structured interviews via an IRB-approved secure platform or in person during the next regularly scheduled clinical visit based on their preference. Interviews will last 20-30 minutes. Parents will help adolescents enter video sessions (we expect most adolescents will be familiar with this process from online schooling during the pandemic). A team member with training in clinical care and research of adolescents and families will conduct the interviews. First, adolescents will be asked to complete validated measures of symptoms [50] and chemotherapy induced alterations in taste [51], say which meal they tried (or considered trying), then answer questions about how that worked for them (or didn't) and recommendations for improvements (nutritional pathway). Parent interviews will focus on logistics (meal selection, ordering, delivery, timing), meal use relative to treatment-related events and associated caregiving demands (time-demands pathway), and allotment adequacy (cost-coping pathway).

---

## **4.2 Recruitment**

Upon IRB approval of the study and requested waiver to access clinical records, we will monitor the clinic schedule for visits by eligible children. A research team member will use EPIC data and referrals from the clinical social workers to identify dyads to contact, connect with the child's oncology provider, and send information about the study to parents via their child's EMR patient portal plus approach the dyad during the clinical appointment. Provided information will be in English and Spanish and include a summary of the study purpose. After completing T1 and T4 surveys and each interview (T2, 3 and 4), the adolescent and the parent will each receive gift cards (\$15 + \$15) for a possible total of \$150 (\$75 for the adolescent + \$75 for the parent) per dyad.

## **4.3 Expected Risks**

The primary risk for this study is psychological stress and breach of confidentiality, which can cause emotional distress or embarrassment. The study team will have processes in place to protect the security of all study data. All staff will have completed the training pertaining to protecting subject data, and all data will be stored on secured servers in password protected files.

---

## 4.4 Time & Events Table

**Table 1: Time & Events**

| Study Assessments                                                                                             | Pre-Study/
Screening  | Baseline (T1)  | MTM-Kids Meal Deliveries  |                 |                  |
|---------------------------------------------------------------------------------------------------------------|--------------------------------------|----------------------------|---------------------------------------|-----------------|------------------|
|                                                                                                               |                                      |                            | 4 weeks
(T2)                       | 8 weeks
(T3) | 12 weeks
(T4) |
| Eligibility Verification                                                                          | ×                                    |                            |                                       |                 |                  |
| Informed Adult Consent/Parent Permission/Adolescent Assent/HIPAA Authorization                    | ×                                    |                            |                                       |                 |                  |
| Equiti Foods Registration                                                                         |                                      | ×                          |                                       |                 |                  |
| Adolescent Survey                                                                                 |                                      | ×                          |                                       |                 |                  |
| - Socio-demographics (5 items)                                                                                |                                      |                            | ×                                     | ×               | ×                |
| - Symptoms (14 items)                                                                                         |                                      |                            | ×                                     | ×               | ×                |
| - Chemotherapy-induced alterations in taste (13 items)                                                        |                                      |                            |                                       |                 | ×                |
| - Acceptability (2 items) and appropriateness (2 items)                                                       |                                      |                            |                                       |                 |                  |
| Parent Survey                                                                                     |                                      |                            |                                       |                 |                  |
| - Socio-demographics (15 items)                                                                               | ×                                    |                            |                                       |                 | ×                |
| - Food (6 items) and nutrition (6 items) insecurity                                                           | ×                                    |                            |                                       |                 | ×                |
| - Financial coping behaviors (18 items)                                                                       | ×                                    |                            |                                       |                 | ×                |
| - Personal Financial Wellbeing Scale (8 items)                                                                | ×                                    |                            |                                       |                 | ×                |
| - Participation in social roles and activities (12 items)                                                     | ×                                    |                            |                                       |                 | ×                |
| - Acceptable (4 items), appropriate (4 items), feasible (4 items), affordable (4 items), accessible (4 items) | ×                                    |                            |                                       |                 | ×                |
| Medical record abstraction                                                                        |                                      | ×                          |                                       |                 |                  |
| Gift Card                                                                                         |                                      | ×                          | ×                                     | ×               | ×                |
| Meal Order and Delivery Process Check                                                             |                                      | ×                          |                                       |                 |                  |
| Interview                                                                                         |                                      |                            | ×                                     | ×               | ×                |

### Footnotes to Time & Events Table

1. Screening includes tests to confirm eligibility.
2. Informed consent will include (a) adult consent from the parent for their participation in the study, (b) parental permission for their adolescent's participation, and (c) adolescent assent. HIPAA authorization to extract a

limited set of data from the adolescent's electronic medical record. Completion of the parent contact form, baseline assessments and Equiti Food account set-up will commence after the written consent/permission/assent have been obtained.

3. Parent participants must register with the Equiti Foods Website in order to select and order MTM allotment. Allotment will be weekly (up to 10 meals per week), for 12 weeks. Delivery will take 3-5 days and parents can order up to 5 working days in advance.
  4. Adolescents will complete surveys at baseline, T2, T3 and T4. See [ADOLESCENT SURVEYS](#)
  5. Parents will complete surveys at baseline and at 12 weeks (T4). See [PARENTAL SURVEYS](#)
  6. A limited set of data (specified in the HIPAA authorization form) about the adolescent's cancer diagnosis, diagnosis date, treatment protocol, treatment initiation date, and treatment exposures to date will be extracted from the adolescent's electronic medical record.
  7. Gift cards will be given following completion of the Baseline and then the 12-week survey, and following completion of the Week 4, 8 and 12 interviews. The gift cards value will be \$15 for parent and \$15 for the child, for a possible total of \$75 for parent and \$75 for child.
  8. Parents will be contacted within 1 week following baseline data collection to verify that they have placed the initial meal order, and problem-solve as indicated.
  9. Semi-structured interviews will be conducted and audio-recorded via an IRB-approved secure video platform, or in-person during a regularly scheduled clinical visit according to the participant's preference. An investigator-developed interview guide will inform the interviews (see [APPENDIX III – Study Semi-Structured Interview Guides](#)).
-

## **5 STUDY POPULATION**

To participate in this study, participants must meet ALL eligibility criteria outlined below.

### **5.1 Inclusion Criteria**

1. Written informed parental permission plus adolescent assent to participate in the study plus HIPAA authorization for release of personal health information.
2. Adolescent is willing and able to comply with study procedures based on the judgement of the investigator.
3. Adolescent is age 12-17 years and can use English for complex communication
4. Adolescent has completed at least one cycle of cancer chemotherapy and expects to undergo at least 2 more cycles.
5. Eligible parents of adolescent subjects:
  - Aged 18 years or older
  - Primary caregiver of a study-eligible adolescent
  - Screens positive for household material hardship (food, nutrition, utility, or transportation insecurity)
  - Uses English or Spanish for complex communications

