## **2 STUDY OBJECTIVES**

### **2.1 Primary Objective**

*2.1.1 To determine feasibility of recruitment and retention for a future efficacy trial of “Medically Tailored Meals-Kids (MTM-Kids)”, a food is medicine intervention to mitigate food and nutrition insecurity for households of adolescents in active treatment with chemotherapy for pediatric cancer*

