### 8.1 Study Design

This feasibility study uses a longitudinal design and multiple methods to determine the possibility of using the MTM-Kids study processes and intervention in a future full-scale RCT. 15 parent/adolescent dyads will be enrolled and asked to complete a survey at baseline (T1), receive MTM-Kids meals over 12 weeks, participate in interviews at 4, 8, and 12 weeks (T2, T3, T4) after starting to receive meals to inform refinement, and complete a follow-up survey at 12 weeks (T4).

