### **8.3.3      *Exploratory Endpoint Analysis***

Descriptive statistics (mean total scores, score ranges, standard deviations) and figures will be used to portray the results of baseline (T1) and 12 weeks (T4) assessments of household food insecurity, household nutrition insecurity, parental financial coping strategies, parental time demands, and parental financial wellbeing.

Descriptive statistics (mean total score, score range, SD) will be used to portray adolescents' treatment-related symptoms and chemotherapy-induced alterations in taste.

Qualitative descriptive approaches will be used to identify themes in the interviews with adolescents and parents about their experiences with MTM-Kids meals and recommendations for needed improvements.

---

Treatment exposures, scores on assessments of symptom and chemotherapy induced alterations in taste will be used to qualitatively explore linkages between symptoms, alterations in taste, and themes in the interview data.

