#### 15.2.2.8 Study Eligibility Screener

We are developing a program to help us support better support families while their child is going through cancer therapy. May I ask you about your basic needs at home to see if you are eligible for this program?

|                                                                                                                                                         |     |    |
|---------------------------------------------------------------------------------------------------------------------------------------------------------|-----|----|
| Is your child between age 12 and 17.9 years?                                                                                                            | YES | NO |
| Has your child received at least one cycle of chemotherapy?                                                                                             |     |    |
| Are at least 2 more cycles of chemotherapy planned for your child?                                                                                      |     |    |
| Has your child reported that food tastes different to them since they started chemotherapy?                                                             |     |    |
| In the last 6 months, did you ever worry that the food would run out before you got money to buy more?                                                  |     |    |
| If you checked YES, would you like help with this?                                                                                                      |     |    |
| In the last 6 months, has your utility company (gas, electric, oil, water) sent you a letter threatening to shut off service for not paying your bills? |     |    |
| If you checked YES, would you like help with this?                                                                                                      |     |    |
| In the last 6 months was there a time when you couldn't pay the rent or mortgage in time because you didn't have the money?                             |     |    |
| If you checked YES, would you like help with this?                                                                                                      |     |    |

|                                                                                                                                                                                         |  |  |

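### Entry counts remaining chemotherapy in cycles, follow-up runs 12 weeks, and treatment status is not recorded after baseline, so later data may include off-treatment adolescents who cannot be identified

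*Protocol*

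**What the plan says.** Criterion 4 in Section 5.1 requires that the "Adolescent has completed at least one cycle of cancer chemotherapy and expects to undergo at least 2 more cycles". The screener in Section 15.2.2.8 asks the same of the parent: "Are at least 2 more cycles of chemotherapy planned for your child". Neither gives a length of time.

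The study clock runs in weeks. Section 4.1 says "The intervention will be 12-weeks duration", and Section 8.1 has dyads "participate in interviews at 4, 8, and 12 weeks (T2, T3, T4) after starting to receive meals to inform refinement". End of chemotherapy is not among the reasons for stopping the intervention (Section 6.1) or for going off study (Section 6.5), so meals and assessments go on after it.

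The primary objective (2.1.1) concerns "households of adolescents in active treatment with chemotherapy for pediatric cancer", and endpoint 3.1.1 uses the same population. The Study Summary instead names patients who have received chemotherapy.

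The secondary endpoint (3.2.1) is rated at week 12. For the exploratory endpoint, Section 8.3.3 says descriptive statistics and "figures will be used to portray the results of baseline (T1) and 12 weeks (T4) assessments of household food insecurity" and the other parent-reported measures. Neither depends on treatment status. Section 8 uses SDs and confidence intervals of change to size the future trial. Section 8.3.3 also plans to relate treatment exposures to symptom and taste scores, which Section 7.2.1 collects only at T2 to T4.

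Table 1 marks medical record abstraction at baseline only, and the form in Section 15.2.1.1 is labelled T1.

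**The concern.** The entry rule and the follow-up schedule use different units, and nothing ties them together. A dyad can meet criterion 4, begin during chemotherapy, and give its T3 or T4 data after chemotherapy has ended.

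Three uses of the data are exposed:

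- **Week-12 acceptability and related ratings.** These are taken at the time point most likely to fall after treatment.
- **The T1-to-T4 change in parent and household measures.** Section 1.2 names illness-related costs and caregiving time as pathways to food insecurity. Both could ease when treatment ends, with or without meals, and a single arm has no comparator to separate the two.
- **The link from treatment exposures to T2-T4 taste and symptom scores.** The exposure data stop at T1, before the first of those scores is taken.

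If status is not captured as the study runs, the planned data will not show which dyads were still on chemotherapy.

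**Working it through.** The protocol states no figure for this point, so there is none to reproduce. The schedule itself is consistent: 3 feedback rounds × 4 weeks = 12 weeks.

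**Inputs**
- Minimum remaining chemotherapy: 2 cycles (Sections 5.1 and 15.2.2.8).
- Assessments: weeks 4, 8 and 12 from the first meals (Section 8.1).
- Time from order to first meal: "Delivery will take 3-5 days" (footnote 3 to Table 1).
- Cycle length: not given. Assumed range 2 to 6 weeks.
- Assumed: exactly two cycles remain and they run back to back from entry.

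**Break-even.** With no lag, chemotherapy ends at week 2 × cycle length. An assessment at week w falls after that if cycle length < w / 2.
- T3: 8 / 2 = 4 weeks.
- T4: 12 / 2 = 6 weeks.

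**Off-treatment share of the 12 weeks** = (12 − (2 × cycle length − lag)) / 12. A lag of one week is an assumption covering ordering plus delivery.

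| Cycle (weeks) | Chemotherapy ends, no lag | T2 / T3 / T4, no lag | Share off, no lag | Share off, 1-week lag |
|---|---|---|---|---|
| 2 | week 4 | boundary / off / off | 67% | 75% |
| 3 | week 6 | on / off / off | 50% | 58% |
| 4 | week 8 | on / boundary / off | 33% | 42% |
| 5 | week 10 | on / on / off | 17% | 25% |
| 6 | week 12 | on / on / boundary | 0% | 8% |

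With the one-week lag, T3 is off treatment at 4-week cycles and T4 is off treatment even at 6-week cycles. Gaps or delays between cycles would move the end of chemotherapy later and work the other way.

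**Possible effect on the change data (illustration only).** Let a fraction f of dyads be off treatment at T4, and let being off treatment shift change by b SDs.
- Shift in mean change = f × b.
- SD ratio = √(1 + f(1 − f)b²).
- Sample-size ratio = 1 + f(1 − f)b².

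With f = 0.33:
- b = 0.5: mean shift 0.33 × 0.5 = 0.17 SD; SD ratio √(1 + 0.221 × 0.25) = 1.027; sample-size ratio 1.055.
- b = 1.0: mean shift 0.33 SD; SD ratio √1.221 = 1.105; sample-size ratio 1.221.

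Both f and b are assumed; the protocol supports no particular value.

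**The case against.** The strongest reply is that this is only a possibility and that little rests on it. Two cycles is a minimum, and adolescents with more or longer cycles stay on treatment throughout. The primary benchmarks in Section 8.3.1 use enrolment, survey completion, deliveries and interviews, not change scores. The T1-to-T4 comparison is exploratory and descriptive, and Section 8 itself warns that effect sizes from small feasibility studies are unreliable. All of this stands, and it limits the point to a modest improvement.

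Some stronger readings are tempting but not supported:

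- **That every objective is restricted to active chemotherapy.** Only the primary objective and endpoint say so. The secondary objective refers to active treatment more generally, and the exploratory objectives state no treatment condition.
- **That the analysis treats T1 and T4 as both on treatment.** The protocol makes no such assumption; it is silent on status.
- **That easing symptoms or taste would produce a false T1-to-T4 signal.** Neither has a T1 value, so mixing can occur only across T2 to T4. Section 1.2 also says taste alteration can last months or years after treatment, which softens the effect on those scores. It does not soften the effect on time demands or cost coping.
- **That continuous chemotherapy would make the change attributable to meals.** A single arm cannot show that in any case.

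It can also be said that the T1 form records the treatment protocol number, current cycle and cycle start date, so planned status at T4 might be worked out, and that the parent interviews touch on treatment events. These help, but they give a plan made at baseline and incidental remarks, not actual status at each later assessment.

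**Conclusion.** The point holds as a gap between the entry rule and the schedule, made worse by a gap in data collection. The rule permits T4 to fall after chemotherapy for cycles under 6 weeks, and T3 for cycles under 4 weeks, when exactly two cycles remain. Those thresholds are arithmetic with no lag. The shares in the table rest on assumed cycle lengths and describe the minimum case, not the expected sample.

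The importance is low to moderate. The primary benchmarks are affected only in which population they describe. The firmer part is that status after T1 is not recorded, so the planned exposure analysis and the change SDs carried to the next trial cannot allow for treatment ending.

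A reader might infer that criterion 4 is wrong and should require 12 further weeks of chemotherapy. The documents do not support that: it would narrow a single-site pool in a study whose primary question is whether recruitment is feasible. Nor should adolescents still on chemotherapy at T4 become the main summary, since that selects on a status arising after baseline.

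**What to change.** 1. Repeat a short medical-record item at T2, T3 and T4: chemotherapy ongoing (yes or no) and date of last dose. Mark it in Table 1 and check that the HIPAA authorization covers it.
2. Keep the all-dyad summary as the main one. Beside it, show T1-to-T4 change, week-12 ratings and T2-T4 taste and symptom scores by chemotherapy status.
3. Reconcile the population wording in the Study Summary, Sections 2.1.1, 3.1.1 and 5.1 and the screener with the 12-week schedule, so that it is clear whether time after chemotherapy belongs to the intended population.

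The cost is one brief abstraction per dyad at each of three time points, at most 15 × 3 = 45 in all, plus a split display. Numbers per group will be very small, so the split is descriptive only. No change to the eligibility rule is needed.
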